** *Outcome Variables* **		
MOUD Use*	Claim for methadone, buprenorphine (including formulation, e.g., sublingual tablets, sublingual film, subcutaneous injection, and implants), XR naltrexone	Medicaid
Adherence to MOUD*	Continued receipt of MOUD (continued methadone program appointments or renewal of buprenorphine or naltrexone prescriptions)	Medicaid
Retention*	Length of stay in treatment episode (in days)	Medicaid
Adverse Event*	SUD-related emergency department visit or hospitalization, including for overdose; increase in SUD level of care	Medicaid
Healthcare Utilization*	All-cause emergency department visits and hospitalizations	Medicaid

Table Notes: OASAS = CDS database; * Time-varying variables

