#### Aim 2: Evaluating program organizational factors influencing OUD treatment retention

This objective focuses on analyzing program organizational characteristics associated with improved medication adherence and retention in OUD treatment among TA adults, while controlling for individual and community characteristics related to retention in care. Employing time-to-event analysis, a set of statistical methodologies focusing on the time until an event occurs, we will focus on a) discontinuation of MOUD use following initiation during the treatment episode and b) treatment completion as our event outcome of interest. To accommodate the longitudinal structure of these data, we will employ extended Cox models. We will assess the validity of the proportional hazards (PH) assumption for time-invariant variables through log-log plots, observed versus expected plots, goodness-of-fit testing, and the use of time-dependent variables. Variables not adhering to the PH assumption will be assessed for interaction with time and, if necessary, incorporated into the final Cox model. We will assume non-informative censoring, meaning that censoring and the event risk are independent after conditioning on observable features.

These models will yield hazard ratios, critical in evaluating the hypotheses stated. To mitigate confounding, we will introduce individual, program, and community-level variables into the model, yielding adjusted hazard ratios alongside point estimates and 95% confidence intervals. The extensive confounding measures at individual, program, and community levels collectively address bias stemming from omitted or uncontrolled confounding variables. We will conduct robust sensitivity analyses and explore variation in association strength due to plausible instruments for program selection, such as patient travel distance to programs and concurrent MOUD use among other individuals in the same community. To prevent overfitting, we will apply techniques outlined in Aim 1. As a sensitivity analysis to consider the multilevel structure of the data, we will deploy extended mixed-effects Cox models. An extended Cox model can incorporate time-dependent factors [99]. A mixed-effects Cox model can incorporate multiple fixed and random effects [100]. Specifically, we will include a fixed effect for each individual, program, and community-level variable defined above and random effects for repeated measures of an individual over time, program, and community.

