#### Aim 3: Examining program characteristics and adverse OUD-related events

Our final objective is to examine the association between treatment program organizational characteristics and adverse OUD-related events (AE) such as an SUD-related emergency department visit, including for overdose, while accounting for individual and community characteristics. Like Aim 2, we will employ time-to-event methods, focusing on the occurrence of the first adverse event. The adjusted hazard ratio of program structural factors, staff characteristics, and clinical care delivery features will be evaluated against a null hypothesis of 1. We will conduct sensitivity analyses akin to those described in Aim 2, ensuring the robustness of our results and conclusions. Applying the Lachin-Foulkes method to a study spanning 14 years, with variable drop-out rates, we determined that our sample size (>65,000) provides substantial power to detect clinically significant associations. Even under variable rates of attrition (10%-70%), we maintain adequate power to detect hazard ratios of 1.15 (or 0.87) with 80% power and a 5% type I error rate. Given the estimated study sample (>65,000), we are powered adequately to detect clinically meaningful associations.

*Aim 3a*: *Program structural factors and AE*. First, we will investigate the relationship between program structural elements (e.g., program size and type) and the occurrence of adverse OUD-related events (AE).

*Aim 3b*: *Program staff characteristics and AE*. Second, we will explore the connection between program staff attributes (e.g., professional degrees) and the incidence of adverse OUD-related events.

*Aim 3c*: *Clinical care process measures and AE*. Third, we will assess how clinical care processes (e.g., use of telehealth, counseling modalities) are associated with the prevalence of adverse OUD-related events.

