We must acknowledge that our study has its limitations. The most critical limitation is that we will not be experimentally controlling for all factors related to program selection. Consequently, we will be tempered in making causal inferences about the associations we find [101, 102]. We address this limitation through the use of the rigorous statistical methods and sensitivity analyses described above. Studies of this type, which examine the impact of organizational quality in real-world settings, have a long tradition in informing both scientific practice and policy [102]. Another limitation of our study is that we do not compare the impact of multi-level factors on MOUD outcomes between TA and older adults, limiting our ability to discern if there are organizational factors that are more or less potently associated with MOUD outcomes for TA adults than for non-TA adults. Still, our study findings will yield important recommendations to engage and retain an underserved population in treatment at a pivotal life phase. Lastly, the administrative databases we use will not identify all aspects of care provision for OUD (e.g., staff decision-making and patient clinical experiences). Nevertheless, our study will be a valuable addition to the growing body of qualitative, ethnographic, and spatially oriented research that explores the impact of various mechanisms like social networks, institutional qualities, and structural vulnerability on substance-related risks and harms and treatment practices [103–105].

Over the past decade, there has been a significant increase in the prevalence of OUD among TA adults. Unfortunately, the existing OUD treatment framework inadequately serves this demographic, with lower rates of evidence-based treatment and increased early treatment attrition. Moreover, the heightened risk of substance-related adversities magnifies the issue. We need research to understand better the impact of existing types of care as well as inform policy makers, treatment providers, and the public about what individual, program, and community characteristics are associated with better quality of care. With the array of care options and the diversity inherent among TA adults, our study’s analytical methods will provide crucial information to address treatment gaps and disparities, benefiting this highly vulnerable age group.

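### Aim 2 credits adjustment for measured covariates with handling omitted confounders, which it cannot do; an unmeasured trait of plausible strength can produce a hazard ratio of the size Aim 3 is powered to detect

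*Protocol article*

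**What the plan says.** The Aim 2 analysis section enters individual, program and community variables into extended Cox models and then states: "The extensive confounding measures at individual, program, and community levels collectively address bias stemming from omitted or uncontrolled confounding variables". The next sentence promises sensitivity analyses and an exploration using possible instruments for program selection: how far patients travel to programs, and MOUD use by others in the same community. Each adjusted hazard ratio is tested against 1.

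The Aim 3 section adopts similar sensitivity analyses and presents them as securing the robustness of its results. It gives the effect size the study can "detect hazard ratios of 1.15 (or 0.87) with 80% power and a 5% type I error rate". Aim 2 gives no target.

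The limitations in the Discussion concede that "we will not be experimentally controlling for all factors related to program selection" and promise restraint about causal inference. They then say: "We address this limitation through the use of the rigorous statistical methods and sensitivity analyses described above".

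**The concern.** The sentence claims a property that regression adjustment lacks. Entering a covariate controls confounding by that covariate and, to some degree, by whatever it closely tracks. Confounders that are omitted stay uncontrolled, however many measured variables are entered. The statement also carries weight, because the Discussion points back to these methods as the answer to what it calls its most critical limitation.

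The Introduction describes patient features that Table 1 does not contain, namely ambivalence about MOUD and family pressure to enter treatment. Either could plausibly influence both which program a person enters and whether they stay, although the article does not say that either one drives program choice.

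The issue matters because the cohort exceeds 65,000 and the detectable hazard ratios are close to 1. A large sample narrows the interval around a biased estimate and does not move the estimate. Patient selection into programs could therefore appear as a precise association between a program feature and retention or adverse events, and be passed on to policy makers.

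**Working it through.** **1. The plan's own power figure.** Inputs from the Aim 3 section: hazard ratio 1.15, 80% power, 5% type I error (two-sided assumed), more than 65,000 patients, 10% to 70% attrition.

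Schoenfeld events for an even split: 4 × (1.960 + 0.842)² / (ln 1.15)² = 1,608. This is 2.7% of the 58,500 left after 10% attrition, or 8.2% of the 19,500 left after 70%. A 10:90 split needs 4,465 events.

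The event rate, exposure split and drop-out hazard are not given, so 80% cannot be reproduced exactly. It is plausible. A Lachin-Foulkes calculation (assumed 13-year accrual in 14 years, even split, 70% cumulative loss) gives power of 0.84 at 0.005 events per year and 0.98 at 0.01. The power statement is not in dispute here.

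**2. Bias from one omitted binary trait.** Let the trait multiply the hazard by RR, with prevalence p1 and p0 in two program types after adjustment. With no program effect, the apparent hazard ratio is about

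(1 + p1(RR − 1)) / (1 + p0(RR − 1)).

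All trait values are assumptions:

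| RR | p1 vs p0 | Apparent HR |
|---|---|---|
| 2.0 | 50% vs 30% | 1.50/1.30 = 1.154 |
| 2.0 | 60% vs 30% | 1.60/1.30 = 1.231 |
| 1.5 | 50% vs 30% | 1.25/1.15 = 1.087 |

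Solving for p1 at an apparent HR of 1.15 with p0 = 20%, p1 = (1.15(1 + 0.2(RR − 1)) − 1)/(RR − 1):

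- RR 1.5: 53%
- RR 2: 38%
- RR 2.5: 33%
- RR 3: 30.5%

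**3. Would such a bias be statistically significant?** Assume 10% of 65,000 have an event (6,500) and an even split. Power = Φ(ln HR × √(6,500/4) − 1.96).

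- HR 1.154: above 99%.
- HR 1.087: 0.0834 × 40.3 − 1.96 = 1.40, about 92%.

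**4. Simulation check.** Cox model, n = 65,000, no true program effect, omitted trait with hazard ratio 2, 20 replicates per setting:

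| Prevalence | Share with event | Fitted HR | HR = 1 rejected |
|---|---|---|---|
| 40% vs 20% | 1.3% | 1.174 | 60% |
| 40% vs 20% | 12% | 1.156 | 100% |
| 40% vs 20% | 58% | 1.147 | 100% |
| 30% vs 20% | 1.2% | 1.084 | 20% |
| 30% vs 20% | 12% | 1.071 | 95% |
| 30% vs 20% | 57% | 1.070 | 100% |

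The formula gives 1.4/1.2 = 1.167 for the first prevalence pair, so it is a fair guide that runs slightly high when events are common.

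**5. E-value for 1.15.** This is the minimum strength, on the risk-ratio scale, that an unmeasured confounder needs with both program type and outcome to explain the estimate fully.

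- Rare event: 1.15 + √(1.15 × 0.15) = 1.57.
- Common event: RR ≈ (1 − 0.5^√1.15)/(1 − 0.5^√(1/1.15)) = 1.10, giving an E-value of 1.44.
- Confidence limit: if 1.15 is estimated at exactly 80% power, SE = ln 1.15/2.802 = 0.0499 and the lower 95% limit is exp(0.1398 − 1.96 × 0.0499) = 1.043, with an E-value of 1.25.

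**6. The instruments.** Table 1 lists among its community variables the distance to prescribers and treatment programs, and the share of Medicaid members with OUD who receive MOUD. These are near-equivalents of the two proposed instruments, and the Aim 2 text says community variables enter the model. Conditioning on them may leave little independent instrument variation. The Introduction also describes longer travel as a barrier in itself, which suggests a path from distance to retention that does not run through program choice.

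**The case against.** The strongest reply is that the article does not ignore unmeasured selection. It plans an instrument exploration immediately after the disputed sentence, extends similar sensitivity analyses to Aim 3, frames both aims as associations, and promises tempered causal inference. This stands. A reader might infer that selection would be reported as a program effect with nothing to reveal it, and the text does not support that. What remains is that none of these elements measures residual confounding, and that the Discussion offers the same methods as the remedy.

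A second reply is that the details of sensitivity analyses belong in an analysis plan that is not shown. That also stands: the absence of an E-value is not an error in a journal article. The point is the sentence itself, which is wrong as printed.

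Third, the numbers are illustrative. A 20-point gap that survives adjustment for a rich covariate set, combined with a doubled hazard, is not trivial, and a 1.5-fold trait at the same gap gives only 1.09. With about 1% of patients having events, significance is far from assured. This stands too, so the claim is that such a trait can produce the effect, not that it does.

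Finally, a reader might count staff decision-making and patient experience, which the Discussion says the data do not capture, as omitted confounders. The article describes them as aspects of care provision. They are mostly features of care after entry and closer to mediators.

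**Conclusion.** The Aim 2 sentence is incorrect: adjustment addresses measured confounding only. The reliance on it in Aim 3 and the Discussion makes it more than a matter of style. Under the assumed values (hazard doubled, 50% versus 30% after adjustment, no program effect) the apparent hazard ratio is about 1.15, equal to the effect Aim 3 is powered to detect. The E-value is about 1.57, or 1.44 for a common outcome.

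The figures do not show that any particular finding will be confounded, that the stated power is wrong, or that 1.15 is a target for Aim 2. Applying it there is an extension, because Aim 2 names no hazard ratio.

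**What to change.** 1. Reword the Aim 2 sentence so that it claims control of measured confounding only, and adjust the Discussion's reference back to it.
2. For each program-factor hazard ratio in Aims 2 and 3, report a quantitative bias analysis: an E-value or a bias-factor table, for the estimate and for the confidence limit nearer to 1. Set it beside the strength of the measured patient covariates as context, not as a rule that blocks a conclusion.
3. State the assumptions behind each instrument, and do not fit its near-equivalent from Table 1 as a covariate in the instrument analysis without giving a reason.

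Table 1 also lists "All-cause emergency department visits and hospitalizations" as an outcome, and its non-SUD part might suggest a negative control. This should be optional and exploratory at most, with no decision rule. Hospital affiliation and integrated mental health licensing could themselves affect non-SUD acute care, and such a control does not fit Aim 2's outcomes of MOUD discontinuation and treatment completion.

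The cost is a wording change and a little further calculation, mostly from estimates already planned. Small hazard ratios will be reported more cautiously.

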Substance use and treatment for SUD occur within a broad social ecological context where the interplay of individual, community, and structural-level (including treatment program organizational) factors impact substance use and SUD treatment outcomes [61, 62]. Factors above the level of the individual, referred to as “social determinants of health,” such as structural racism and poverty, are potent fundamental causes of health inequalities [63].

TA adults have distinct individual-level characteristics that affect treatment engagement [4, 6, 64, 65]. They are more likely to have family members pressuring treatment [4, 64, 66, 67], and/or be involved with the criminal justice system [4, 26, 68, 69]. Criminal justice agencies and actors (e.g., judges and correctional staff) historically have been opposed to MOUD, preferring instead to rely on non-pharmacologic, non-evidence-based treatment approaches [70–73]. Furthermore, barriers to engagement, including lack of transportation or treatment programs that are high threshold settings, requiring frequent attendance at clinics and participation in highly structured protocols, challenge TA adults [60, 65, 67, 74–76]. TA adults are generally at ease interacting through modern telecommunications [6], with emerging shifts in telehealth that were prompted initially by the COVID-19 pandemic now offering new opportunities for treatment tailoring for this age group [77].

TA adults’ response to treatment also is affected by community-level factors that influence health and how they may engage with systems of care [78]. Variation in use of MOUD is associated with community social capital and local availability of programs offering MOUD [79]. MOUD is less available outside urban areas and often requires longer travel times that can be a barrier [74–76]. TA adults often contend with peers who use substances, local easy availability of substances, residential instability, hostile experiences with local law enforcement, and a lack of public transportation [80, 81]. Many TA adults from marginalized communities grapple with disparities in access and quality of care due to socioeconomic privation, racial/ethnic segregation and discrimination, and long-held community mistrust of medical and other institutions [67, 82–86].

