** *Community-level Characteristics* **		
Access	Distances to the nearest Medicaid MOUD prescriber and other addiction treatment programs; low threshold buprenorphine programs; harm reduction providers or drug user health hubs providing MOUD services	Medicaid
Community Resources	Social vulnerability index (SVI) (i.e., composite measure of area-level vulnerability to adverse outcomes); racial/ethnic composition of community; population density; density of OUD among Medicaid members; proportion of Medicaid OUD members receiving MOUD	Census Medicaid

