#### Aim 1: Quantifying associations between MOUD use and social and ecological factors

To quantify the associations between MOUD use (e.g., methadone, buprenorphine, XR naltrexone) and individual, community, and treatment program organizational characteristics, we will use generalized linear mixed effects models (GLMM). The primary outcome of interest is whether an individual received MOUD during the treatment episode. We will include random effects to account for repeated measurements within individuals and clustering by program and county, and time fixed effects to address secular trends, such as the pre- and post-COVID-19 periods. We will test whether models can be simplified by replacing time fixed effects with time-related splines or power terms. We also will explore interactions among variables of substantive interest (e.g., varying the effect of criminal justice involvement on OUD treatment by community influences and program organizational factors). We will adopt a generalized estimating equations approach with robust standard errors to ensure the robustness of our findings. To address potential bias associated with correlations between predictors and random effects, we will utilize the Mundalk approach of mean-centering variables within county. A penalization approach (lasso regression) will be used for feature selection to address overfitting and collinearity. The validity of the approach will be ensured using cross-validation and sample splitting. Given the large sample size (>65,000) across multiple years, we are powered to detect conservative odds ratios (≥1.1) with 80% power at a two-sided alpha of 0.05 (assuming 10% overall prevalence of MOUD use). Higher prevalence will lead to improved power.

*Aim 1a*: *Associations with psychological and social determinants of health*. First, we will explore the association between MOUD use and psychological and social determinants of health at both the individual (e.g., housing status, comorbid mental health diagnoses) and community levels (e.g., social vulnerability index, program availability). For each group of measures, we will build distinct GLMMs. These models will be adjusted for age, sex, race, as well as other individual baseline and time-varying covariates (as specified in the measures table).

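### The instruments proposed for program selection have a direct path to care and near-match model covariates; separately, the Aim 1 Mundlak step omits the program level.

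*Protocol article*

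**What the plan says.** **Instruments.** The Aim 2 analysis section plans sensitivity analyses that explore how association strength varies with "plausible instruments for program selection, such as patient travel distance to programs and concurrent MOUD use among other individuals in the same community". The Aim 3 section says its own sensitivity analyses will be akin to these.

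**The same kind of variables as covariates.** Table 1, Community-level Characteristics, lists "Distances to the nearest Medicaid MOUD prescriber and other addiction treatment programs" under Access and "proportion of Medicaid OUD members receiving MOUD" under Community Resources. On the main Cox model, the Aim 2 section says: "To mitigate confounding, we will introduce individual, program, and community-level variables into the model". On the mixed-effects Cox model, it says: "we will include a fixed effect for each individual, program, and community-level variable defined above".

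**Direct paths.** The Introduction states that "MOUD is less available outside urban areas and often requires longer travel times that can be a barrier". It also says that community-level factors affect how these patients respond to treatment.

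**Centering.** The Aim 1 model has random effects for individual, program and county. To deal with correlation between predictors and random effects, it uses the Mundlak "approach of mean-centering variables within county". A GEE analysis is added as a robustness check.

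**The limitation.** The Discussion gives as its most critical limitation that "we will not be experimentally controlling for all factors related to program selection". It adds that the methods and sensitivity analyses already described address this, and that causal claims will be tempered.

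**The concern.** Two separate problems bear on how far the results can be trusted where patients are not randomly distributed over programs.

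First, calling a variable an instrument for program selection asserts that it reaches retention or adverse events only through the program attended. Travel burden plausibly affects whether a patient keeps coming to any program. Table 1 defines methadone adherence by continued program appointments, which makes that path concrete. Community MOUD use plausibly reflects local norms and services that act on the individual whichever program is attended. If these variables also sit in the outcome model as covariates, nothing is excluded and they carry no instrumental information. Agreement between such a check and the main Cox model could then be read as reassurance it does not give.

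Second, the Mundlak step is meant to break the correlation between predictors and random effects. Centering at county level does this for the county effect only. If programs in the same county differ both in patient mix and in unmeasured propensity to use MOUD, patient-level odds ratios in Aim 1 keep part of that between-program difference.

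**Working it through.** The article states no figure to reproduce on this point. Every effect size below is assumed, the true effect is set to 0, and linear models stand in for the logistic and Cox models.

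**1. Matching the roles**

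| Variable | Instrument (Aim 2) | Covariate (Table 1) | Direct path (Introduction) |
|---|---|---|---|
| Distance | Travel distance to programs | Distance to nearest prescriber and programs | Travel time as a barrier |
| Community MOUD use | Concurrent use by others in the community | Share of Medicaid OUD members on MOUD | Community factors affect response |

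The distance entries are close but not identical (programs in general against the nearest). The community MOUD entries are nearly the same quantity.

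**2. Error of an instrument with a direct path.** Let Y = βD + δZ + U and D = πZ + V, where Z is independent of U and V. The IV estimand is Cov(Y,Z)/Cov(D,Z) = β + δ/π, so the bias is δ/π. Simulated two-stage least squares bias at N = 65,000 (unadjusted regression bias in brackets):

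| Direct effect δ | π = 0.2 | π = 0.3 | π = 0.5 |
|---|---|---|---|
| 0 | 0.00 (0.12) | 0.01 (0.11) | 0.00 (0.10) |
| 0.02 | 0.10 (0.12) | 0.06 (0.12) | 0.04 (0.11) |
| 0.05 | 0.24 (0.12) | 0.17 (0.12) | 0.10 (0.12) |
| 0.10 | 0.50 (0.13) | 0.33 (0.13) | 0.20 (0.13) |

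Of the nine cells with a direct path, the instrument is worse than no adjustment in five and better in four. The direction depends on δ and π, and the article gives neither.

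**3. The instrument also kept as a covariate.** Three parameters are needed (intercept, Z, D). The instrument set {Z, intercept, Z} has rank 2, so the effect of D is not identified.

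**4. Centering by county only.** Assume county effect c and program effect u, each with variance 1, a patient covariate x = 0.5c + 0.5u + e, and Y = 0.3c + 0.3u + e′, with 62 counties and 600 programs.

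- Uncentered: (0.15 + 0.15)/(0.25 + 0.25 + 1) = 0.20; simulated 0.198.
- County-centered: with 600/62 ≈ 9.7 programs per county, about 0.9 of the variance of u lies within counties. The bias is 0.9 × 0.15/(1 + 0.9 × 0.25) = 0.11; simulated 0.108.
- Program-centered: simulated 0.001.

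These fits have no program random effect, so they correspond to the GEE check with independence weighting.

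**5. With a program random effect.** The random-intercept model gives between-program information the weight ψ = σ²ₑ/(σ²ₑ + nσ²ᵤ) = 1/(1 + 0.09n). That is 0.69 at n = 5 and 0.10 at n = 100. Fitted models left a bias of about 0.11 at 5 patients per program, 0.06 at 20, and 0.01 to 0.02 at 100. With the program mean of x added, the estimate was within about 0.003 of zero at all three sizes. Under the assumed 600 programs, the average size is 65,000/600 ≈ 108.

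**The case against.** **No IV estimator is promised.** The article speaks of exploring variation in association strength and names no two-stage method. It also does not say that a variable used as an instrument stays among the covariates in that same analysis. This stands: the rank result in step 3 holds only if both roles are kept in one model. But labelling the variables as instruments for program selection already asserts exclusion. Stratifying on variables that affect the outcome directly is no cleaner test.

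**Proximity as an Aim 1c predictor.** A reader might infer that this alone disqualifies distance as an instrument. It does not. Aim 1c concerns choice of medication, and exclusion is specific to the outcome.

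**The barrier sentence is about access.** It concerns availability, not retention after entry. This is fair for that sentence, but the Introduction also gives community factors an effect on treatment response.

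**Mundlak centering was not offered as a defense against program selection.** Correct: it is stated in Aim 1 for correlated random effects, and Aim 2 carries over only the overfitting techniques. It is therefore a separate point here. County centering is not useless; it took 0.198 to 0.108 in step 4. Table 1 also holds some program aggregates (share of transition-age clients, of OUD clients, and of OUD clients on MOUD), though not means of most patient covariates.

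**Conditioning on an instrument-like variable can amplify residual bias.** True where the direct path is negligible. Where one is stated, omitting the variable leaves confounding, so keeping it as a covariate is the more defensible choice.

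**Conclusion.** The point holds as two limited corrections. The proposed instruments have direct paths by the article's own account and overlap the covariates, and their roles are not separated. A check built on them could not be taken as evidence against selection bias. Its error is δ/π, of unknown size.

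A reader might go further and put the error at 20 percentage points of retention, for example 2 points of direct effect over a 10-point first stage (0.02/0.10 = 0.20). The documents supply neither number, and the plan reports hazard ratios, so no such figure is supported. Nor do they support saying that every safeguard against selection fails: the primary analysis is covariate-adjusted Cox regression, and the Discussion undertakes to be tempered about causation.

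For Aim 1, county-only centering leaves correlation with program effects inside counties. Under the assumed effects this matters most for small programs and in the GEE check, which has no program effect. In the mixed model it is slight where programs contribute around 100 patients each.

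Both corrections should be made before analysis. The status section reports that none had been done.

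**What to change.** **Aim 1.** Add program-level means of the patient covariates alongside the county means, in both the mixed model and the GEE analysis. Do not center the exposures fully within program: that would remove all variation in time-constant program characteristics, which Aim 1b sets out to study. For those characteristics the added means adjust for measured patient mix only; unmeasured selection remains.

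**Aims 2 and 3.** Keep nearest distance and community MOUD share as covariates and stop calling them instruments. If an IV check is wanted, use differential distance (distance to the nearest program with the feature minus distance to the nearest without it), adjusted for distance to the nearest program. State the exclusion assumption and exclude the instrument itself from the outcome model. Otherwise report E-values for the main hazard ratios.

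**Cost.** Some wording and a few derived variables. Differential distance is likely to be a weaker instrument, so that check will be less precise.
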